### Exclusion criteria

We will exclude individuals who change the type or dosage of their medicines during the intervention, those that are not willing to continue intervention, and individuals who suffer from probable complications related to soy milk consumption. Figure 1 shows the study flowchart.

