### Non-inclusion criteria

Patients will not be included if they (1) changed type or dosage of their medicines over the last 3 months; (2) were hospitalized in the last 3 months; (3) were diabetics or were affected by celiac or other gastrointestinal diseases including cancers and infectious diseases; (4) were pregnant or lactating; (5) consumed antibiotics, pre- or probiotic products, multi-vitamin, and mineral supplements during the last 3 months; and (6) were current smokers.

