### Sample size calculation

Considering the type I error of 5% (*α* = 0.05) and type II error of 20% (*β* = 0.20, power = 80%) and fecal concentrations of calprotectin as the key variable, we manually, without the use of any software, calculated required sample size using the following formula [30]:
$$ n=\frac{2\left[{\left(a+b\right)}^2\times {\upsigma}^2\right]}{{\left({\mu}_1-{\mu}_2\right)}^2} $$

*n* = sample size in each group.

*μ*_1_ = mean for fecal calprotectin in the intervention group (we considered it as 424 μg/g based on the study of Morshedzadeh et al. [31]).

*μ*_2_ = mean for fecal calprotectin in the control group (which was considered as 602 μg/g based on the study of Morshedzadeh et al. [31]).

σ = variance (SD) for mean concentrations of calprotectin, which was considered as 141 (the average SDs reported for fecal calprotectin in the control and intervention groups of Morshedzadeh et al.’s study [31]).

*a* = conventional multiplier for alpha = 0.05 that was 1.96.

*b* = conventional multiplier for power = 0.80 that was 0.842.

Overall, based on the formula and given a 50% drop-out in each group, we will need a sample size of 15 persons for each group. Due to frequent visits (about 6 visits) that each participant would have throughout the study, we considered the drop-out rate as much as 50%. However, we would try our best to keep the drop-outs as low as possible.

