### Study design and intervention

The diagram for Standard Protocol Items: Recommendations for Interventional Trials (SPIRIT) is shown in Fig. 2. After recruiting participants, participants will be stratified based on age (20 to 40 and 40 to 60 years), gender (male/female), BMI (18.5 to 24.9 and 25 to 30), and type of medicines (anti-inflammatory and immunosuppressant) into different blocks and will be randomly allocated to the intervention or control groups. For each patient in a certain block, a matched person in terms of abovementioned variables would be placed in that block. Then, these two patients in a given block would be randomly assigned to the intervention and control groups. To do randomization, an identification code will be given to each eligible patient, and then, code of patients with the same age, gender, BMI, and medication will be stated in the lottery container, and finally, patients with the same conditions will be randomly assigned to the intervention or control groups. Random allocation will be done by a person who is unaware about the aim of our study. Patients in the intervention group (*n* = 15) will receive 250 mL/day preservative-free soy milk along with routine treatments that they were taking for their condition. Participants in the control group (*n* = 15) will receive only routine treatments. The intervention will last for 4 weeks. The assessment of primary and secondary outcome variables will be done at the study baseline and end of trial. Participants in both groups will also receive usual dietary recommendations for IBD patients based on European Society for Parenteral and Enteral Nutrition (ESPEN) guideline [32]. This guideline will be explained to patients by an experienced nutritionist. Given that preservative-free soy milk will be expired within 12 days after production, three 1-L bottles of soy milk will be delivered to patients in intervention group every 12 days (at the study baseline, day 12, and day 24). At the study baseline and day 12, patients in the intervention group will received 3 1-L bottles of soy milk (used during 12 days), and at day 24, they will received 2 1-L bottles of soy milk (used during 8 days). Due to the unfavorable taste of soy milk, patients in intervention group will be asked to consume it at night before sleep. They should consume a 250-mL glass of soy milk every night. Participants will be instructed in a class, prior to the start of trial, about the quantity of soy milk they have to consume in a day. A standard glass (which contained 250 mL soy milk) will be shown to participants, and all will be asked to use the same glass to make sure that the daily portion they are consuming is the one the investigators requested. To control this, participants will be contacted every day and they will be asked to send us the photo of the glass they are using for soy milk drinking. At each delivery of soy milk bottles, patients will be monitored for soy milk consumption and will be asked to give back the empty bottles. Participants’ compliance will be assessed using the following formula: (number of used packages/all given packages) × 100. In addition to assessment of compliance, consumption of soy milk will be monitored by phone call every week. In addition, collecting three 1-day dietary recalls from participants throughout the study can further help computing the compliance to soy milk intake. Participants will be asked not to change their lifestyle, dietary habits, and medicines during the study.

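### The protocol excludes randomised patients for events after allocation, one of which can occur only in the soy-milk arm, so the comparison is no longer protected by randomisation

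*Protocol article*

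**What the plan says.** The protocol article has three separate lists. Inclusion criteria and Non-inclusion criteria settle who may enter, and the second already deals with earlier medication changes: "Patients will not be included if they (1) changed type or dosage of their medicines over the last 3 months". Exclusion criteria then covers what happens later: "We will exclude individuals who change the type or dosage of their medicines during the intervention, those that are not willing to continue intervention", and also "individuals who suffer from probable complications related to soy milk consumption".

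Under Study design and intervention, patients are matched in twos and "these two patients in a given block would be randomly assigned to the intervention and control groups". Controls "will receive only routine treatments", so they have neither soy milk nor a placebo. The same section states: "The intervention will last for 4 weeks". Outcomes are taken at baseline and at the end.

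Assessment of variables lists fecal calprotectin, disease severity and disability among the primary outcomes. Statistical analysis plans t tests on changes and an ANCOVA adjusted for baseline. It does not say that excluded patients are followed or analysed.

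**The concern.** A medication change during the four weeks, a decision to stop, and a soy-related complication can each be seen only after a patient has been allocated. Each may also go with the outcome. A medication change may mark worsening disease, and a complication in a patient with bowel disease may overlap with the symptoms being scored.

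The reasons do not bear equally on the two arms. No control can have a complication of soy milk. Unwillingness to continue may also fall more on the soy arm, because Study design and intervention acknowledges that the product tastes unpleasant. Patients left after such exclusions are no longer the groups that chance created, and losing one patient leaves a matched partner without a counterpart. Adjusting for baseline removes only the part of the selection that baseline values explain.

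At stake is the validity of every between-group comparison, including the primary outcomes. The loss cannot be repaired once the end-of-trial samples have gone uncollected.

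**Working it through.** **Inputs from Sample size calculation.** Means 424 and 602 μg/g (difference 178), SD 141, multipliers 1.96 and 0.842, 15 per group.

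**The plan's own figure.** n = 2 × (1.96 + 0.842)² × 141² / 178² = 2 × 7.851 × 19,881 / 31,684 = 9.85, so 10 per group. The stated 15 is 10 × 1.5. The bias calculation below uses 15 randomised per arm and SD 141.

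**Assumptions.** The documents give neither exclusion rates nor the link between exclusion and outcome. Let f be the proportion excluded and ρ the correlation between the tendency to be excluded and final calprotectin, with normal values. With φ the standard normal density and z the (1 − f) quantile, the mean of those kept shifts by −ρ × SD × λ, where λ = φ(z)/(1 − f).

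**1. Exclusion in the soy arm only, no true effect.** For f = 0.20, z = 0.842 and λ = 0.280/0.80 = 0.350, so 141 × 0.350 = 49.3 μg/g before multiplying by ρ.

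| f | Spurious benefit, ρ = 0.3 | ρ = 0.5 | ρ = 0.7 |
|---|---|---|---|
| 10% | 8 μg/g | 14 | 19 |
| 20% | 15 μg/g | 25 | 35 |
| 50% | 34 μg/g | 56 | 79 |

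Simulated two-sided type I error (t test, 15 per arm randomised, nominal 5%):

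| f | ρ = 0.3 | ρ = 0.5 | ρ = 0.7 |
|---|---|---|---|
| 20% | 5.7% | 7.3% | 9.1% |
| 50% | 7.5% | 13.4% | 22.1% |

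Most of these false positives favour soy milk; at the higher values nearly all do.

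**2. Upper bound.** If exclusion takes exactly the worst soy patients, removing 3 of 15 shifts the mean by 0.326 SD (0.326 × 141 = 46 μg/g), with type I error about 16%. Removing 5 of 15 shifts it by 0.516 SD (73 μg/g), with type I error about 28%.

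**3. Medication change in both arms, same threshold, 20% excluded in control.**
- No true effect: both arms lose the same kind of patient, and the bias is 0.
- True effect 178: fewer soy patients cross the threshold (11% at ρ = 0.3, 7% at ρ = 0.5, against 20% of controls). λ in the soy arm falls to 0.213 and 0.145. The bias is 0.3 × 141 × (0.350 − 0.213) ≈ 6 μg/g and 0.5 × 141 × (0.350 − 0.145) ≈ 14 μg/g, both **against** soy milk.

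**4. Both mechanisms together, true effect 178 (simulated, ρ = 0.3 and 0.5).**

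| Medication change (control rate) | Soy-only | Net bias |
|---|---|---|
| 20% | 20% | about 8 μg/g toward soy at both ρ |
| 20% | 10% | 2 toward soy to 2 against |
| 30% | 5% | 3 to 12 against soy |

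The sign depends on rates that the documents do not state.

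**The case against.** The strongest reply is that the article never says whether exclusion means removal from the analysis or only from the intervention, and that an analysis plan not shown here may define the analysis set. That is fair, and it limits certainty. But the rule stands beside the eligibility lists, removal is its natural reading, and the Statistical analysis section does not bring these patients back. If only stopping the product was meant, the wording still permits removal.

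Four stronger readings are tempting, and the documents do not support them.

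- **That the rule as a whole favours soy milk.** Only the soy-complication reason points that way, and only if those patients do worse. Medication change can occur in either arm and can also be a reduction. Stopping because of taste need not go with high calprotectin.
- **That half the patients would be removed under this rule.** The protocol writes "we considered the drop-out rate as much as 50" per cent, but as a planning allowance for both groups that it attributes to the number of visits. It also says that it will try to keep losses low.
- **That poor tolerability would be hidden.** The Adverse events section has patients report, and investigators record, any event during the study. What may be lost is those patients' efficacy data.
- **That the false-positive rate would be 16 to 28%.** That requires exclusion to be fixed entirely by outcome and confined to one arm. Patients enter on stable therapy and are followed for four weeks, so even a 20% outcome-related exclusion is an assumption.

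The illustration also uses an unadjusted t test, not the planned baseline-adjusted ANCOVA, so it gives an order of magnitude only.

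**Conclusion.** The concern holds in limited form. The protocol fixes post-randomisation exclusions that are plausibly related to outcome, one of which is possible only in the soy arm. If followed as written, they can bias the comparison. This is a stated rule that needs correcting, not a detail left out.

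Net direction and size are unknown. With soy-only exclusion of 20%, correlation 0.3 to 0.7 and no true effect, the spurious benefit is roughly 8 to 20% of the planned difference (15/178 to 35/178), with modest inflation of the type I error. The 46 to 73 μg/g obtained by removing the worst 3 to 5 soy patients is an upper bound. With medication-change exclusions added, the bias can shrink, vanish or reverse. That uncertainty does not make the rule safe, because the rates that would decide the sign could be seen only after the fact.

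**What to change.** Reword the Exclusion criteria section so that, in place of exclusion:

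- medication changes, stopping and probable soy-milk complications are recorded and reported by arm;
- every randomised patient who agrees is still asked for the end-of-trial blood, stool and questionnaires, whether or not the product was stopped;
- the primary analysis includes all randomised patients in their allocated group, and a per-protocol set is secondary only;
- withdrawals of consent are counted by arm, and their missing end values are examined in a sensitivity analysis.

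This leaves any rule on stopping the product as it is. The cost is the rewording plus contact, sampling and assays for patients who stopped, within the 30 planned. The price in interpretation is that non-adherence and changed medicines may dilute the estimated effect or otherwise alter the outcomes; the per-protocol set and the by-arm reporting let a reader judge this.

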**Fig. 1 Fig1:**
[figure not shown]
Study flowchart

All participants will read the terms and conditions written in an informed consent (Supplementary file, section A), and optionally, they can accept to participate in the current trial. The ethics committee of Tehran University of Medical Sciences approved the study. Moreover, this clinical trial was registered in the Iranian Registry of Clinical Trials (www.irct.ir) on 27 January 2019 with code number of IRCT20181205041859N1.

### Sample size calculation

Considering the type I error of 5% (*α* = 0.05) and type II error of 20% (*β* = 0.20, power = 80%) and fecal concentrations of calprotectin as the key variable, we manually, without the use of any software, calculated required sample size using the following formula [30]:
$$ n=\frac{2\left[{\left(a+b\right)}^2\times {\upsigma}^2\right]}{{\left({\mu}_1-{\mu}_2\right)}^2} $$

*n* = sample size in each group.

*μ*_1_ = mean for fecal calprotectin in the intervention group (we considered it as 424 μg/g based on the study of Morshedzadeh et al. [31]).

*μ*_2_ = mean for fecal calprotectin in the control group (which was considered as 602 μg/g based on the study of Morshedzadeh et al. [31]).

σ = variance (SD) for mean concentrations of calprotectin, which was considered as 141 (the average SDs reported for fecal calprotectin in the control and intervention groups of Morshedzadeh et al.’s study [31]).

*a* = conventional multiplier for alpha = 0.05 that was 1.96.

*b* = conventional multiplier for power = 0.80 that was 0.842.

Overall, based on the formula and given a 50% drop-out in each group, we will need a sample size of 15 persons for each group. Due to frequent visits (about 6 visits) that each participant would have throughout the study, we considered the drop-out rate as much as 50%. However, we would try our best to keep the drop-outs as low as possible.

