**Methods:**

This study is a randomized clinical trial, in which thirty patients with mild to moderate severity of UC will be randomly allocated to receive either 250 mL/day soy milk plus routine treatments (*n* = 15) or only routine treatments (*n* = 15) for 4 weeks. Assessment of anthropometric measures and biochemical indicators including serum concentrations of high-sensitivity C-reactive protein (hs-CRP), tumor necrosis factor-α (TNF-α), interleukin-1β (IL-1β), and interferon gamma (IFN-γ) will be done at the study baseline and end of trial. In addition, the quantity of butyrate-producing bacteria including *Clostridium* cluster IV, *Faecalibacterium prausnitzii*, and *Roseburia* spp.; prebiotic bacteria including *Lactobacillus* spp. and *Bifidobacteria* spp.; and mucus-degrading bacteria including *Akkermansia muciniphila*, *Bacteroides fragilis*, and *Ruminococcus* spp., as well as calprotectin and lactoferrin levels, will be explored in fecal samples. Also, the *Firmicutes* to *Bacteroidetes* ratio which is of significant relevance in human gut microbiota composition will be assessed.

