### Statistical analysis

The Kolmogorov-Smirnov test will be used to examine normal distribution of variables. Log transformation will be conducted for the non-normally distributed data. To examine differences in qualitative variables between soy milk and control groups, we will use the chi-square test. We will apply the independent sample *t* test to detect differences in quantitative variables between the soy milk and control groups. In addition, mentioned test will be used to compare between-group changes in outcome variables. To do within-group comparison, we will use the paired-sample *t* test. Multivariate analysis of covariance (ANCOVA), as a general linear model, will be used to examine the effects of soy milk consumption on outcome variables. In this analysis, baseline value of outcome variables and potential confounding variables which are different between the intervention and control groups will be adjusted to avoid potential risk of bias and detect independent results. All statistical analyses will be done using the SPSS software version 18 (SPSS, Inc. Chicago, IL, USA). *P* < 0.05 will be considered significant.

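### The 10 evaluable patients per group behind the stated sample size give about 76%, not 80%, power for the planned t test, and averaging two SDs can only add to the shortfall

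*Protocol article*

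**What the plan says.** Under Sample size calculation, the protocol takes fecal calprotectin as the key variable and uses n = 2(a+b)²σ²/(μ₁−μ₂)² per group.

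- **Multipliers:** a is the "conventional multiplier for alpha = 0.05 that was 1.96" and b the "conventional multiplier for power = 0.80 that was 0.842".
- **Means:** for the intervention group, "we considered it as 424 μg/g based on the study of" a cited earlier study; for the control group, a mean "which was considered as 602 μg/g based on the study of" that same study.
- **σ:** 141, labelled as variance and SD at once and described as "the average SDs reported for fecal calprotectin in the control and intervention groups" of that study. The two SDs themselves are not given.

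The result of the formula is not printed. The section goes straight to the final figure: "given a 50% drop-out in each group, we will need a sample size of 15 persons for each group".

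Under Statistical analysis, the independent-sample t test is planned "to detect differences in quantitative variables between the soy milk and control groups" and to compare changes between groups. A baseline-adjusted ANCOVA is also planned.

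**The concern.** Two shortcuts enter the number before drop-out is considered, and both make it smaller.

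1. The multipliers 1.96 and 0.842 are normal quantiles, whereas the planned test refers to a t distribution. In large trials the difference is negligible. At 10 per group it is not.
2. The formula uses σ². When two groups have different SDs, the matching quantity with equal group sizes is the mean of the two variances. Averaging the SDs and then squaring gives a smaller value unless the SDs are equal.

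What is at stake is the claim of 80% power. The printed 15 per group is built on the formula's result, and the Limitations section defends the trial's size by reference to the computed number.

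**Working it through.** **Inputs (Sample size calculation).** α = 0.05, two-sided as implied by 1.96; power 0.80; means 424 and 602, difference 178; σ = 141; drop-out 50%.

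**Step 1: reproduce the plan's figure.**

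n = 2 × (1.96 + 0.842)² × 141² / 178² = 2 × 7.851 × 19,881 / 31,684 = 9.85, rounded up to 10 per group.

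10 × 1.5 = 15, the printed figure. Dividing by (1 − 0.5) would give 20, so 15 is reached only by multiplying. The base of the plan is therefore 10 evaluable per group.

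**Step 2: power of the planned t test at that base.** With n per group, the degrees of freedom are 2n − 2 and the noncentrality is 178 / (141 × √(2/n)). At n = 10 these are 18 and 2.823, and the two-sided critical value is 2.101 instead of 1.96.

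| Evaluable per group | Power, normal approximation | Power, t test |
|---|---|---|
| 10 | 80.6% | 76.1% |
| 11 | 84.2% | 80.4% |
| 15 | 93.3% | 91.6% |

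So 11 per group are needed where the formula gives 10. This step needs no assumption beyond the protocol's own inputs.

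**Step 3: averaging SDs.** Let r be the ratio of the two source SDs, with their mean fixed at 141. The root-mean-square SD is 141 × √(1 + ((r − 1)/(r + 1))²). It equals 141 if r = 1 and is larger otherwise. The protocol does not give r, so every value above 1 below is an assumption. The value 1.42 is 602/424, the ratio if the SDs scaled with the means.

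| Assumed r | Root-mean-square SD | Protocol's formula | t test: n for 80% | t-test power at 10 | t-test power at 15 |
|---|---|---|---|---|---|
| 1 | 141.0 | 9.85 | 11 | 76.1% | 91.6% |
| 1.25 | 141.9 | 9.97 | 12 | 75.6% | 91.2% |
| 1.42 | 143.1 | 10.15 | 12 | 74.9% | 90.8% |
| 2 | 148.6 | 10.95 | 12 | 71.7% | 88.6% |
| 3 | 157.6 | 12.32 | 14 | 66.6% | 84.7% |
| 4 | 164.4 | 13.40 | 15 | 62.9% | 81.6% |

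Two thresholds follow. The protocol's own formula passes 10 once r exceeds about 1.28. Power at 15 evaluable per group falls below 80% only once r exceeds about 4.7.

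**The case against.** The strongest reply is that the trial randomises 15 per group, not 10. A reader might infer from the shortfall at 10 that the trial misses 80% power even with no drop-out. The documents do not support that. Ten evaluable already means that a third were lost; with no loss, t-test power is 91.6% at SD 141 and 84.7% even at an assumed SD ratio of 3. This part of the reply stands. It does not dispose of the point, because the protocol assigns the margin above 10 to an anticipated 50% drop-out and so cannot also count it as cover for an understated base.

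Second, the protocol never prints 10. That is true, but 10 follows from its formula and inputs, and 10 × 1.5 gives exactly the printed 15.

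Third, the formula is an openly stated textbook approximation, and the exact correction is one patient per group. This stands, and it is why the point is minor.

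Fourth, the SD error cannot be sized. This also stands. It may be zero, and at a ratio of 2 it raises the SD by only 5.4% (148.6/141). A reader might take the larger ratios in the table as likely; nothing in the documents says so.

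Fifth, baseline-adjusted ANCOVA could recover power. At 10 per group and SD 141, an assumed baseline–outcome correlation of 0.35 gives about 81% with 17 degrees of freedom. But the protocol states no correlation and its calculation makes no use of one, so the 80% claim cannot rest on it. The shortfall is accordingly stated for the unadjusted t test only.

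**Conclusion.** The point holds as a minor correction. On the protocol's own inputs, the 10 evaluable per group implied by the formula give 76.1% power for the planned unadjusted t test, about 4 percentage points below the stated 80%; 11 per group give 80.4%. This part rests on a two-sided α of 0.05, a difference of 178 and a common SD of 141, all from the protocol.

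The averaging of SDs is a method error in a known direction but of unknown size: none if the SDs are equal, and one further patient per group (12 instead of 11) at an assumed ratio of 2.

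The finding concerns the stated evaluable number and its power. It does not show that the trial is underpowered if all 15 per group are evaluable. The drop-out step in the same section is a separate and larger error: at the anticipated 50% loss, 7 to 8 per group remain, with t-test power of 58.4% to 65.2% at SD 141. That shortfall should not be added to the weight of this point.

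**What to change.** 1. Replace 141 with √[(SD_control² + SD_intervention²)/2], using the two SDs from the cited study, and print both SDs. Label σ as a standard deviation.
2. Compute the evaluable number with the noncentral t distribution.
3. State that number before the drop-out step. Give either at least 11 evaluable per group for 80% power (more if the SDs differ: 12 already at a ratio of 1.25), or the power that 10 evaluable deliver, which is at most about 76% unadjusted.
4. If the sponsor prefers to rely on the baseline-adjusted ANCOVA, state the assumed baseline–outcome correlation and its source, and base the calculation on it.

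The cost is one recalculation and a few corrected sentences, with a slightly less favourable figure than the one now claimed. This point alone requires no change to recruitment, design or analysis.

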### Limitations

Despite using validated questionnaires for assessment of dietary intakes, disease severity, disabilities, and quality of life, misclassification of participants cannot be fully excluded. Furthermore, change in gut microbiota during the sample collection phase is the most important concern for investigators. To avoid this, we will collect fecal samples in the laboratory and keep it immediately at − 70 °C. In addition, we would try our best to have all the fecal samples in the lab within the 2 h after sampling; however, some samples might arrive within > 2 h. One might argue that the sample size would be inadequate for this study; however, it must be kept in mind that several highly cost variables including six inflammatory biomarkers and 9 genes for quantitative real-time polymerase chain reaction (qRT-PCR) are supposed to be quantified in this study. Due to limited funding in developing countries, performing the study with a sample size greater than the one computed for this study would not be affordable for researchers. In addition, most studies on microbiota or fecal calprotectin have been done with a similar sample size [70–73].

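### Fifteen per group does not absorb a 50% drop-out: 7 to 8 completers remain, with about 60% power by the planned t test instead of 80%

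*Protocol article*

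**What the plan says.** The Sample size calculation section bases the trial on one outcome, "fecal concentrations of calprotectin as the key variable". It prints the standard two-means formula for the number per group and all its inputs: a two-sided 5% error rate ("conventional multiplier for alpha = 0.05 that was 1.96"), 80% power ("conventional multiplier for power = 0.80 that was 0.842"), means of 424 and 602 μg/g, and an SD of 141.

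It then moves directly to its conclusion: "given a 50% drop-out in each group, we will need a sample size of 15 persons for each group". Neither the formula's result before the allowance nor the inflation step is shown. The reason given for the high loss is the number of visits, about six per patient: "we considered the drop-out rate as much as 50" per cent. The section adds that the investigators will try to keep losses low.

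The Abstract and the Study design and intervention section fix 15 patients per group. The Limitations section defends that size on cost, saying that "performing the study with a sample size greater than the one computed for this study would not be affordable for researchers".

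**The concern.** A drop-out allowance should leave the required number of evaluable patients after the assumed loss. Losing half of 15 leaves 7.5 per group, so 15 is right only if the formula asks for 7 or 8. With the printed inputs it asks for 10.

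Calprotectin is the only outcome used to size the trial, and 80% is the only power figure given. A reader who accepts that figure would treat a non-significant calprotectin result as stronger evidence against an effect than a trial losing half its patients could supply. The Limitations section compounds this by treating 15 per group as the computed requirement, when the computation points to 20.

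**Working it through.** **Inputs** (all from Sample size calculation, except the test, which is from Statistical analysis)

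- Multipliers: a = 1.96 and b = 0.842, so a + b = 2.802
- Means: 424 and 602 μg/g, a difference of 178
- SD: 141, so the standardised difference is 178/141 = 1.26
- Drop-out: 50% in each group
- Planned test: independent-samples t test

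**Step 1. The formula's result.**
n = 2 × (2.802² × 141²)/178² = 2 × (7.851 × 19,881)/31,684 = 9.85, rounded up to 10 evaluable per group.

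**Step 2. Reproducing the stated 15.**

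- Multiplying by (1 + drop-out): 10 × 1.5 = 15 (unrounded, 9.85 × 1.5 = 14.8, again 15). This matches.
- Dividing by (1 − drop-out): 10/0.5 = 20 (unrounded, 9.85/0.5 = 19.7, again 20). This does not match.
- One-sided 5% variant: n = 7.76, and 7.76/0.5 = 15.5, rounded up to 16. This is close, but the printed multiplier of 1.96 rules it out.

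The multiplication by 1.5 is therefore an inference, since the step is not printed. It is the only route found that agrees with 1.96 and gives 15.

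**Step 3. Completers under the stated assumption.**
15 × (1 − 0.5) = 7.5 per group, against 10 required.

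**Step 4. Power at a difference of 178 and SD 141, two-sided 5%.**
The normal approximation is Φ(1.26 × √(n/2) − 1.96). The t-test column uses the noncentral t distribution.

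| Completers per group | Normal approximation | t test |
|---|---|---|
| 7 | 66% | 58% |
| 7 and 8 (normal: 7.5 each) | 69% | 62% |
| 8 | 71% | 65% |
| 10 | 81% | 76% |
| 11 | 84% | 80% |
| 15 | 93% | 92% |

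If each patient independently has a 50% chance of dropping out, t-test power averaged over the possible numbers of completers is 59%.

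**Step 5. Difference detectable with 80% power.**

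- t test: 230 μg/g with 7 per group and 212 with 8
- Protocol's formula: 141 × 2.802 × √(2/n) = 211 with 7 and 198 with 8

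Both ranges lie above the planned 178.

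**Step 6. Drop-out that 15 per group can absorb.**

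- To keep 10: 1 − 10/15 = 33%
- To keep the 11 that the t test needs: 1 − 11/15 = 27%

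**The case against.** Four points can be made for the protocol.

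- **Mixed methods.** The 80% comes from a normal approximation, while the 58% to 65% comes from the t distribution. Like for like, the protocol's formula gives 66% to 71%, and even its own 10 completers give only 76% by t test. This stands as a point of presentation: about 60% is the figure for the planned test, and part of its distance from 80% comes from the approximation and not from drop-out. Power is still below 80% by both methods.
- **The shortfall is conditional.** Fifty per cent reads as a cautious upper figure, and the investigators intend to do better. With losses up to one third, 10 completers remain and the formula's 80% holds; with no losses, power is 92% to 93%. This is correct. But 50% is the rate the protocol adopts and justifies for sizing the trial, and the 80% is claimed at that rate.
- **Baseline-adjusted ANCOVA is planned.** Adjustment could recover power. The protocol gives no baseline-to-final correlation and the formula takes no credit for one. As an assumption only, and treating 141 as an unadjusted SD, correlations of 0.3 to 0.6 would give about 62% to 77% with 7 per group and 69% to 83% with 8 (ignoring the degree of freedom spent on the covariate). Only the most favourable corner reaches 80%.
- **The Limitations section already concedes that the size may look inadequate.** It does, and its argument is about cost. Affordability can justify enrolling 30 patients; it does not support 80% power with half of them lost.

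**Conclusion.** The concern holds. The protocol's own inputs require 10 evaluable patients per group, and a 50% loss then requires 20 per group, or 40 in total. The stated 15 is 5 per group short, which is too much for rounding. At the stated drop-out, power is 58% to 65% by the planned t test and 66% to 71% by the protocol's approximation.

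This rests on the printed means and SD, a two-sided 5% test, loss of about half in both groups, and analysis of completers. The last is consistent with the Exclusion criteria section, which removes patients who change medication, stop the intervention or have complications related to soy milk. It takes no credit for covariate adjustment. The design can stay as it is, but the power statement is wrong as written and must be corrected.

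**What to change.** Keep 30 patients and replace the concluding statement in Sample size calculation with text along these lines:

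> The formula gives 10 evaluable patients per group. Randomising 15 per group allows for 33% drop-out (27% if 80% power is required for the t test, which needs 11 per group). If drop-out reaches 50%, 7 to 8 patients per group remain, and power to detect 178 μg/g is about 60% by t test (66% to 71% by the normal approximation).

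In Limitations, say that 15 per group was set by funding and falls below the 20 per group that the calculation gives at 50% drop-out.

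The cost is wording only, with no change to recruitment, design or analysis. The price is a less favourable power statement. If the 80% at 50% drop-out is to be kept as a claim, the formula requires 20 per group, which the Limitations section indicates is not affordable.
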